#### Monitoring of project activities performed by community health workers

Process monitoring approach using structured and unstructured observations methods was used to assess if activities were implemented as per study protocol. Unstructured observations mainly focused on behavior of treatment activities if participants were asked or instructed to take food/meal prior to drug intake or coming to diagnosis and treatment points after taking meals. In addition, the process monitoring focused on assessing if treatment procedures were followed, the praziquantel dose pole was used properly, recording any adverse events was done, and how CHWs managed any reported adverse effects. A trained observer and field coordinator were involved in process monitoring.

### Quality assurance plan

The CHWs in both arms were supervised after every one weeks by field-based supervisors and observers to detect and correct any deviations from the protocol. During the visit, the supervisor and observer assessed completeness of data captured in the booklets, adherence to inclusion criteria, filling consent forms, performance of POC-CCA tests, PZQ drug administration to participants, POC-CCA test storage condition and assessment of the tests. After every two weeks during the study time, a review meeting was conducted to address any challenges. All treatment registers were reviewed and CHWs with any challenge/problem received support and re-training. The accuracy of CHWs in performing the POC-CCA test was assessed at each visit.

The questionnaires which was used for the study, was developed and piloted in 70 participants from villages outside the study villages. The focus of the piloting activity was mainly to check for reliability of the questions. Field research assistants were trained on how to administer the questionnaire. For the qualitative data collection, an experienced social scientist was involved in training research assistants on the objectives of the study, how to take notes and how to conduct focus group discussions. Discussion guidelines were piloted to ensure that the meaning of the questions was clear to participants. Some questions were adapted from previous studies [31, 32]. All the FGD were recorded using digital recorders after obtaining consent from participants. The FGD were conducted in the Kiswahili language and after data collection, transcription and translation into English language was done. Selected transcriptions were checked to ensure quality of the transcription and translation and was shared with the team of social scientists for critical review.

### Data management and analysis

Some parts of the open checklist were coded before entered in the computer for analysis. Collected data were double entered using CSPro and the final data set were stored in MySQL database. Data were screened for consistency and errors corrected. Data analysis will be done using Stata version 15 (Stata Corp, College station, Texas, USA). Descriptive statistics will be used to describe participant’s demographic information. Assessment of uptake of praziquantel treatment will be done by comparing proportion of the outcomes between clusters in the two arms. For the intervention arm, treatment coverage will be assessed based on number of individuals tested and received treatment after diagnosis as registered in the booklets. For the control arm, coverage for praziquantel treatment will be assessed from the CHWs booklets/registers.

Odds ratios (OR) and 95% confidence interval (CIs) will be calculated using random effect logistic regression analysis adjusting for clustering. For assessing safety and accurate use of CCA test by CHWs, percentage of total steps, crucial steps and no-crucial steps performed correctly will be calculated for each observation cycle and a generalized estimating equation (GEE) logistic regression model for panel data will be fitted to identify factors associated with correct performance of at least 90% of the total steps. In addition, pooled mean and median percentage for reading of the 20 photographic results will be calculated for each observation cycle.

Descriptive statistics will be calculated of FGD participant’s demographic variables and socio-economic characteristics. The narratives during the FGD were recorded using a digital audio recorder, transcribed verbatim in the language of the study participants (Kiswahili) and translated into English. This was followed by verification for accuracy by a second social scientist fluent in Kiswahili and English. The transcripts generated were then imported into ATLAS ti, version 8 and qualitative data analysis was done according to procedures described previously [32]. The focus of the analysis was to reflect thematic description using the principle of interpretative phenomenological analysis (IPA) [33]. The goal of IPA was to explore insiders’ opinions and beliefs related to their experience of a particular phenomenon [33]. Using this strategy, themes were considered to be direct representations of the phenomenon under study [33]. Such approach gives an opportunity to explore social cognition and assumes that one’s interpretations of her experiences reflect the true nature of phenomenon [33]. In our case, the focus was in the experience of CHWs on using the CCA kits and provision of treatment after diagnosis, what were the challenges during MDA, what were the opportunities and what were the perspectives of the participants on the exercise, participants trust of the results and their recommendations to improve the MDA exercise with and without a diagnostic component. A guide was used to stimulate the discussion and the discussion focused on their experience on using the CCA kits and provision of treatment after diagnosis, what were the challenges during MDA, what were the opportunities and what were the perspectives of the participants on the exercise, participants trust of the results and their recommendations to improve the MDA exercise with and without a diagnostic component. Guided by this approach, coding for identified themes was done using a three phase coding system. In the first phase of coding, the primary social scientist performed an initial scan of the transcripts imported in the ATLAS t.i. software and establish initial themes. In the second phase, the social scientist focused in connecting themes and finding link in the data. The third phase, the primary social scientist re-read the data and assign excerpts which illustrated the final themes. Narrative text were applied around the themes, with quotes used to illustrate the text and communicate its meaning to the reader [33].

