**Methods:**

This is a randomized control community trial in which 30 clusters were randomly assigned to either an intervention or control arm to evaluate two interventions on treatment coverage and compliance with treatment. In each cluster, 150 adult participants were enrolled. Community Health Workers (CHW) in both arms were trained on all aspects of praziquantel (PZQ) distribution and management of mild side effects. In the intervention arm, CHWs had additional training on how to use POC-CCA to diagnose intestinal schistosomiasis. In the intervention arm, participants were tested using POC-CCA test for presence of intestinal schistosomiasis and treated based on test results, while in the control arm, participants were treated with PZQ without testing. The primary outcome measure was the proportion of participants provided with PZQ between the two arms and geographical clusters. Secondary outcomes were prevalence of *S. mansoni* infection based on the POC-CCA test conducted by CHWs, ability of CHWs to use the POC-CCA test accurately and safely and community acceptability of the POC-CCA test results from CHWs. Both quantitative and qualitative techniques have been used to collect data at study endpoint.

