**Fig. 2 Fig2:**
[figure not shown]
Flow diagram of trial design and number of sub-villages

**Table 1 Tab1:** Summary of the study profile

Study design	Cluster randomized controlled community trial
Intervention	Community health workers testing for *Schistosoma mansoni* infection using Point-of-care Circulating Cathodic Antigen test before offering treatment
Control	Mass drug administration using praziquantel without testing for *Schistosoma mansoni* infection as per current practice
Primary outcome	Proportion of study participants provided with praziquantel drug (treatment coverage) and geographical cluster (a service area of the community health workers) in the intervention and control arms
Cluster eligibility criteria	Having more than 60 adult individuals served by two community health workers
Inclusion	Individuals aged ≥18 years residing in a study cluster (s), willing to participate and give written informed consent
Exclusion	Pregnant women at the time of treatment, history of adverse reaction to praziquantel and acutely ill at the time of treatment
Sampling eligibility criteria	Residents of the selected clusters or residents of Kome island
Sampling exclusion criteria	Non-resident of the cluster or Kome island as identified by community health workers participating in the study
Sample size per arm	Total sample size (*N* = 4500), Intervention arm (n = 2250) and control (*n* = 2250)

To assess CHWs ability to use the POC-CCA test safely and accurately in the intervention arm, a trained observer (a laboratory technician) visited the study cluster at two, four and six weeks post-training and used a checklist to assess CHWs compliance to safety procedures (Table 2).

**Table 2 Tab2:** Shows the steps required to correctly and safely prepare a Circulating cathodic Antigen rapid diagnostic test

S/no	The steps required to correctly and safely prepare a circulating cathodic antigen test (Critical steps in noted boldface type)	Score
1	Prepare the diagnostic table (cover it with a plastic cover), assemble new test, pippete and gloves	
**2**	**Put on a pair of gloves**	
3	Provide participants with new urine container (s) and instruct them on how to collect urine sample(s) using the provided container	
4	Recording participants demographic information (name, age, sex and village of residence) in the registry when submitting urine sample (s) at the diagnostic table	

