### Sample size

The sample size was estimated using a simplified formula by Hayes and Bennet for cluster randomized trials [28], with a power of 80% to detect an absolute difference in proportion of adult individuals participating in mass drug administration of 25% (50% versus 75%) between the two arms with alpha of 5% and assumed coefficient of variation of 0.3616. The coefficient of variation of 0.3616 was used to account for unequal cluster size. In the intervention arm, we take 75% as level of treatment coverage recommended by WHO at community level [9]. A minimum estimated sample of 150 individuals for each cluster for 30 clusters giving an overall total of 4500 individuals (2250 interventions, 2250 controls) were needed to answer the research questions assuming the standard deviation between clusters of 0.226. For this study, cluster was defined as the service population of the community health worker.

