#### Praziquantel treatment coverage and drug inventory

In both arms, CHWs were provided with praziquantel drugs, praziquantel dose pole and treatment registry books. In the registry book, CHWs in the intervention arm, recorded the POC-CCA test results, the number of tablets/pills provided to each of the participant(s) based on the test results and any reported side effects. In the control arm, CHWs recorded the number of tablets/pills provided to each study participant and any side effects reported by participants.

Diagnosis of intestinal schistosomiasis and provision of PZQ drugs was done at an agreed site within a cluster. Tablets were swallowed under direct observation (DOT) of CHWs. Estimation of number of PZQ tablets given to each participant was done using the praziquantel dose pole, based on the height of an individual (Fig. 7). Study participants who experienced any mild adverse side effects were counselled at the treatment premises and cases with severe adverse effects, were referred to the nearby health facilities.

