
### Ethical clearance and consent to participate

The study was approved by the joint Ethical and Review Committee of Bugando Medical Centre and Catholic University of Health and Allied Sciences (CREC/200/2017). The study received further clearance from the region, district administrative authorities and village authorities. Kiswahili translated informed consent forms were used to obtain consent from study participants. Before recruiting study participants, CHW describes the objective of the study to participants, the benefits and any involve risk for them to participate in the study. For illiterate participants, a thumb print was used to sign the consent forms after a clear description of the study objectives was given to participants. Further permission was requested from study participants and CHW to include their pictures/images during publication of the study findings. All pictures present in this methodology section of the study have received permission from all the study participants and the CHW involved in the study. The trial is number PACTR201804003343404 registered at Pan African Clinical Trial Registry.

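### The trial is powered on participation among all adults, but coverage is measured among consented participants recruited after allocation, so differences in attendance are not captured

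*Protocol article*

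**What the plan says.** **What was planned on.** The Sample size section claims "power of 80% to detect an absolute difference in proportion of adult individuals participating in mass drug administration of 25% (50% versus 75"%). It takes the 75% from the WHO recommendation for coverage at community level. The Hypothesis, aims and objectives section likewise expects coverage of adults to rise above that target.

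**What is measured.** Table 1 and the Primary outcomes section define coverage as the share of study participants who were given praziquantel.

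- Table 1 requires participants to be "willing to participate and give written informed consent", and the Study population section places consent before enrolment.
- On recruitment, the ethics section says: "Before recruiting study participants, CHW describes the objective of the study to participants".
- The Abstract says: "In each cluster, 150 adult participants were enrolled". The Sample size section calls 150 a minimum.
- Testing and treatment take place at one agreed site per cluster, and "Tablets were swallowed under direct observation (DOT) of CHWs".
- In the control arm "coverage for praziquantel treatment will be assessed from the CHWs booklets/registers". In the intervention arm coverage rests on people tested and treated, also as entered in the booklets. The booklets hold the details of study participants. Table 2, step 4, makes the intervention-arm entry when the person hands in urine.

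**What else is known.** Adult population size per CHW was used for randomisation and for the 60-adult eligibility rule (Trial summary). It is not named as a coverage denominator.

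**The concern.** The planned effect and the measured outcome refer to different populations. The 50% and 75% describe adults in a community, including those who never come to the distribution site. The outcome describes adults who have already agreed to take part. The adults whose low uptake motivates the trial are those most likely to be missing.

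Two consequences follow. First, if testing works by bringing more people forward, that gain falls outside the outcome; with 150 enrolled in every cluster, the number enrolled does not show it either. Second, the people in the denominator are chosen after allocation by the worker who delivers the allocated strategy, so the two arms may enrol different kinds of adults. The planned random-effects logistic regression allows for correlation within clusters; it does not correct for selection into them. At stake is what the primary result means and whether it can be set against the 75% target.

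**Working it through.** **1. The plan's own figure.** Inputs from the Sample size section: p0 = 0.50, p1 = 0.75, m = 150 per cluster, 80% power, "alpha of 5% and assumed coefficient of variation of 0.3616", and "assuming the standard deviation between clusters of 0.226". Sidedness is not stated; two-sided is used here.

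Hayes-Bennett formula, clusters per arm:

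c = 1 + (1.960 + 0.842)² × [p0(1−p0)/m + p1(1−p1)/m + k²(p0² + p1²)] / (p0 − p1)²

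- Binomial part: (0.25 + 0.1875)/150 = 0.0029
- Between-cluster part: 0.3616² × (0.25 + 0.5625) = 0.1062
- c = 1 + 7.849 × 0.1092/0.0625 = 14.71, rounded up to 15
- 2 × 15 × 150 = 4500, as stated; power at 15 per arm is 80.8%
- 0.226/0.3616 = 0.625, the mean of 0.50 and 0.75, so the two variability figures agree

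The arithmetic is right for participation among adults. The question is whether that quantity is observed.

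**2. Splitting coverage.** Let a be the share of eligible adults who attend and consent, and u the share of those enrolled who are then covered. Coverage of eligible adults is a × u. The registers give only u.

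Suppose u is the same in both arms (assumed; not given in the protocol):

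| u, both arms | a for 50% (0.50/u) | a for 75% (0.75/u) | Difference in registers |
|---|---|---|---|
| 80% | 62.5% | 93.8% | 0 |
| 90% | 55.6% | 83.3% | 0 |
| 98% | 51.0% | 76.5% | 0 |

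A true 25-point difference between communities then leaves no trace in the outcome.

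**3. Room left for a difference.** If u differs, the largest possible rise over control is 1 − u(control):

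| u in controls (assumed) | Largest possible rise |
|---|---|
| 75% | 25 points |
| 80% | 20 points |
| 90% | 10 points |
| 95% | 5 points |

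So 25 points is out of reach only if uptake among enrolled controls exceeds 75%.

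**4. The numerator.** Table 2, step 14, has test-negative participants advised no treatment, and the primary objective concerns adults diagnosed with infection, a group the control arm does not identify. If receipt of praziquantel is counted over all adults, intervention coverage cannot exceed the test-positive share. At an assumed 60% positive, with full attendance and acceptance, it is at most 60%; at 40% it is 40%, at 90% it is 90%. Changing the denominator alone would therefore leave the arms not comparable.

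**5. If registers stopped at 150.** In an assumed cluster of 300 eligible adults, 50% participation is 150 and 75% is 225. If recording ended at 150, both arms show 150/300 = 50%. A larger denominator would not recover the difference.

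**The case against.** The strongest case on the other side is that the text does not show the planned difference to be unobservable, and most of that case stands.

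- **A reader might infer that the 25 points cannot appear because nearly every enrolled control is treated.** The protocol gives no such figure. Observed swallowing confirms intake among those who accept; it does not make a consenting adult accept. The discussion-group guides (Tables 4 and 5 sections; community questions in Table 4) ask participants whether they agreed to take, or did swallow, the tablets.
- **A reader might infer a cap of 150.** The Sample size section calls it a minimum, and no stopping rule is stated.
- **A reader might infer that 150 per cluster is incompatible with 50% participation.** With 38,062 people in 80 sub-villages (476 each) and an assumed 45–55% adults, there are 214–262 adults and 107–131 participants at 50%. With the earlier 53 sub-villages (718 each) there are 323–395 adults and 162–198 participants, and the conclusion reverses. Selected clusters also need not be average.
- **A reader might infer that exclusions applied at treatment make the denominators differ by arm.** The Study population section excludes such people from the study in both arms, and nothing says that test-negative participants escaped screening.
- **Table 1 has sampling rows, so participants could have been drawn before attending.** This is possible, but the rows give only residency, and a sample restricted to those who consent still drops refusers.
- **An article condenses.** That would excuse an unstated detail. Here the outcome, the consent rule, enrolment and the data source are all stated, and they do not match the planned quantity.

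**Conclusion.** The point holds in a limited form. The Sample size and Hypothesis sections concern participation or coverage among adults in the community; the outcome and analysis sections measure receipt among consented participants listed by CHWs. The attendance and consent part of the planned 25-point difference is not measured. Recruitment after allocation by workers who know the strategy can bias what remains. That they know it is not written, but follows from their delivering it; that biased recruitment occurred is not shown.

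The size of the loss depends on uptake among enrolled adults, which is not given. It is the full 25 points if that uptake is equal in both arms, and less if testing also raises acceptance among those enrolled. The sample size is correct for its inputs, but its 80% power does not carry over to the outcome as defined. This should be settled before the primary analysis, because it determines what the result can be said to show.

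**What to change.** 1. **One denominator for both arms:** eligible adults in the CHW's service population, using the adult counts already held for eligibility and randomisation. If fieldwork still allows, use a random sample from a list fixed before allocation. Count non-attenders and refusers as not covered.
2. **Reconcile the numerator.** Over that same denominator, report separately (a) the proportion reached by the assigned strategy: tested, and treated if positive, in the intervention arm, or treated in control; and (b) the proportion given praziquantel. State which is primary and align it with the primary objective.
3. **If registers stopped at 150 per cluster,** population coverage cannot be recovered. Label the primary result as receipt among consenting participants, do not compare it with 75% or claim the stated power for 50% versus 75%, and acknowledge post-allocation recruitment as a source of bias.

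**Cost.** A revised outcome definition and one adult count per cluster, already held in some form. Coverage figures will be lower and will depend on the accuracy of those counts, which are of adults and may include some who meet an exclusion. The number of clusters is little affected by cluster size: the formula gives 14.89 per arm at m = 100 and 14.62 at m = 200, both rounding to 15.

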**5**	**Receive urine sample from participant (s) label the container with participants identification number and place it in a sample collection dish**	
**6**	**Take Point-of-Care circulating cathodic antigen test kit (s), label it with participants (s) identification number which is similar to the one written on the urine container**	
7	Place the labelled point-of-care circulating cathodic antigen test kit on the table (level surface)	
**8**	**Take the urine container with identification number similar to the one labelled on the point-of-care circulating cathodic antigen test kit and collect urine sample using the enclosed pipette and pour 1–3 drops of urine sample in a test kit well**	
**9**	**Dispose the used pippete in a waste bucket immediately after pouring the urine sample in a test kit**	
**10**	**Dispense 2–3 drops of clearing buffer if provided in a sample well**	
**11**	**Wait for 15–20 min before reading the POC-CCA test result (either positive or negative)**	
**12**	**Read the result correctly (either negative or positive)**	
13	Record the result of the POC-CCA test in the participant register book	
14	Give the test result (s) to participants, and based on the test result, advise them (either to take treatment if results are positive or no treatment if negative)	
15	Dispose of used gloves, desiccant, wrappers and used test kits.	

The bolded sentences shows the most critical steps during preparation and use of the point-of-care circulating cathodic antigen test

At baseline, a quantitative questionnaire was used to collect data on CHW’s and community member’s (heads of households) knowledge about schistosomiasis, the previous community-based MDA strategy, acceptability to be diagnosed for intestinal schistosomiasis by CHWs and treatment with PZQ without being diagnosed for the targeted infection. At the end of the study, qualitative Focus Group Discussions (FGDs) were conducted to assess the experiences of CHWs from both arms after participating in the trial. FGDs were held with selected community members who participated in the study to assess community acceptability and attitudes towards use of POC-CCA test by CHWs.

Randomization of clusters to either intervention or control arms was based on the population size of the adult individuals served by a community health worker. All CHWs serving clusters with less than 60 adult populations were excluded from the study.

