### Secondary outcomes

Secondary outcomes are:-Community Health Workers (CHWs) ability to use the POC-CCA rapid test accurately and safely.Community members acceptability (these are people’s perceptions and attitude on the two-treatment approach) of the POC-CCA test results offered by community health workers.Experience of Community Health Workers on the use of the POC-CCA rapid diagnostic test.Prevalence of *S. mansoni* infection based on the POC-CCA test conducted by Community Health Workers.

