#### Assessment of safety and accuracy of the circulating cathodic antigen (CCA) test performed by community health workers

A trained observer visited each of the CHW in the intervention arm at one, two and six weeks post-training and used a standardized checklist (Tables 4 and 5) to assess the performance of each CHW in adhering to safety procedures and procedures of performing the test, interpretation of the test results and recording of the test result. The observer also collected all the tests kits used within the week and sent them to a second observer to evaluate the test results. In addition, the field observer took a photograph of 20 POC-CCA tests with positive, negative and invalid result to assess CHWs ability to read CCA test accurately.

Observers were trained on how to use the check list and instructed on how to minimize observer bias. Using the checklist, the observer noted if CHWs performed each step correctly and also noted if she/he missed observing any step. The steps were divided into two parts, (i) those critical to safety and (ii) accurate performance of the test. Safety was defined as correctly wearing gloves, use of new urine container for every participant and disposal of the urine containers in approved buckets and urine samples in the toilet immediately after use. Whereas accuracy was defined as following all the necessary steps correctly to arrive at a correct diagnosis (i). Collecting urine samples in an enclosed pipette and pouring it in a test kit well (ii). Dispensing 2–3 drops of clearing buffer into the sample well (if provided by the manufacturer) (iii). Waiting for 15 min before reading test results (iv). Reading test results correctly (v). Recording the results. At each observation, the observer recorded number of POC-CCA rapid test performed since the previous visit and collected the used test kits, number of positives and number of treated participants. In addition, the observer recorded any challenges or concerns experienced by CHWs.

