## Discussion

The overall aim of the present study is to document the additional role of the community health workers to use the point-of-care circulating cathodic antigen test to diagnose community members participating in mass drug administration for intestinal schistosomiasis. The study focused on the adult population who are currently not included in the on-going national MDA exercise, and who are known to have very low compliance to treatment [16]. The introduction of a diagnostic component in the community-based MDA exercise is expected to improve the uptake of praziquantel drugs among adult individuals. This will have a positive impact by reducing the risk of transmission of the disease.

Secondarily, the study will demonstrate the ability of the CHWs to use the POC-CCA safely and accurately. During training, majority of the CHWs demonstrated ability to interpret and differentiate POC-CCA test kits with positive and negative results. However, they had challenges in identifying invalid and unused POC-CCA test, which necessitated re-training. In addition, through the use of CHWs to diagnosed intestinal schistosomiasis using the POC-CCA test(s), the study will allow precise estimate of the prevalence of intestinal schistosomiasis among adult individuals in the study setting.

The inclusion of qualitative studies will help to acquire knowledge about the community perceptions and CHWs experiences after participating in the study. The focus for the community is to understand their acceptability of the diagnostic component performed by CHWs and recommendation to improve the exercise. Community acceptability is crucial for sustainability of any health intervention. Learning from CHW’s experiences, challenges and recommendation after implementing the study will help in improving the ways to integrate diagnostic component to community-based MDA run by CHWs in endemic areas.

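### Community health workers' reading of the 20 photographed tests is summarised only as a pooled percentage, which cannot show which kind of reading error was made

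*Protocol article*

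**What the plan says.** One of the secondary outcomes is the community health workers' (CHWs') "ability to use the POC-CCA rapid test accurately and safely" (Secondary outcomes). For the reading part, the section on assessing safety and accuracy says that "the field observer took a photograph of 20 POC-CCA tests with positive, negative and invalid result to assess CHWs ability to read CCA test accurately". It does not say how many of the 20 belong to each class.

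The stated analysis, in Data management and analysis, is that a "pooled mean and median percentage for reading of the 20 photographic results will be calculated for each observation cycle". No section gives a result by class, a sensitivity or specificity, or an agreement table, either for the photographs or for the used kits that are collected and re-read.

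Two places show what depends on the reading:
- Step 14 of Table 2 has the CHW advise the participant "either to take treatment if results are positive or no treatment if negative".
- Another secondary outcome is the prevalence of *S. mansoni* "infection based on the POC-CCA test conducted by Community Health Workers".

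The Discussion reports of the CHWs in training that "they had challenges in identifying invalid and unused POC-CCA test, which necessitated re-training".

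**The concern.** The three possible reading errors have different consequences. A missed positive means that an infected adult is advised not to take treatment, and it lowers the prevalence estimate. A negative read as positive means treatment that the test did not call for, and it raises the estimate. An invalid test taken as a result means that a decision rests on no information. A percentage correct gives all three the same weight and reports only their total.

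The protocol's own training experience was of difficulty with particular kinds of kit, so a summary that cannot point to a class misses the feature most worth knowing. At stake is whether a conclusion that CHWs read the test accurately can be tied to the decisions that the test drives.

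**Working it through.** **The plan's own figure.** The article gives no numerical target or expected value for photograph reading, so there is nothing to reproduce.

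**Inputs.** 20 images in three classes (Assessment of safety and accuracy); summary by pooled mean and median percentage (Data management and analysis); class sizes not stated, so they are assumed below and varied.

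**1. Direction is lost for any mix.** Let the set hold P positive, N negative and I invalid images, with P + N + I = 20. If a reader misreads a, b and c of them respectively, then

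percent correct = 100 × (20 − a − b − c) / 20.

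Only the sum a + b + c enters. One equation cannot recover three class-specific results.

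Illustration with an assumed mix of 9 positive, 9 negative and 2 invalid:

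| Errors | Overall | Positives correct | Negatives correct | Invalids correct |
|---|---|---|---|---|
| 2 missed positives | 18/20 = 90% | 7/9 = 78% | 100% | 100% |
| 2 false positives | 18/20 = 90% | 100% | 7/9 = 78% | 100% |
| both invalids missed | 18/20 = 90% | 100% | 100% | 0/2 = 0% |

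All three readers get the same planned score.

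**2. How high the score can be with a whole class misread.** For a class of k images, all wrong, the score is 100 × (20 − k)/20:

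| k | 1 | 2 | 3 | 4 | 5 | 6 | 7 | 10 |
|---|---|---|---|---|---|---|---|---|
| Score | 95% | 90% | 85% | 80% | 75% | 70% | 65% | 50% |

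Three classes of nearly equal size have 6 or 7 images each, which gives 65 to 70%. A high individual score beside a failed class therefore needs a class of one or two images.

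**3. The median across CHWs.** Table 1 gives 2250 participants in the intervention arm and Sample size gives 150 per cluster, so 2250/150 = 15 clusters. At two CHWs per cluster (Table 1) that is 30 CHWs, assuming that all are assessed. Assume 2 invalid images, with 14 CHWs misreading both and nothing else. Then the mean is (16 × 100 + 14 × 90)/30 = 95.3% and the median is 100%. The median stays at 100% as long as fewer than half of the CHWs make any error.

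**4. An analogy from the protocol's data.** The Table 3 marks, as printed, are 100, 100, 100, 100, 97, 93, 100, 80, 100 and 70. Their mean is 940/10 = 94.0% and their median 100%, while negative kit 118 scored 80% and the unused kit 70%.

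**5. The checklist.** Correct reading is also step 12 of 15 in Table 2. A CHW who fails only that step scores 14/15 = 93.3%, above the 90% criterion used in the regression model. Step 12 records whether the reading was correct, not which way it was wrong.

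**The case against.** The best counter-argument is that this is a condensed article. It names one descriptive summary among others and does not rule out a breakdown by class in a fuller plan. Pooled may also mean pooled over CHWs rather than over classes. Both points are fair, but the article does fix this summary for this measure, and no class-specific result appears under either meaning of the word.

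Several stronger readings are tempting, and the documents do not support them:
- **That the photographs are the only direct measure of reading with a planned analysis.** Checklist step 12 is a critical step, and the planned step percentages and regression model include it. What it lacks is direction.
- **That CHWs could score near-perfectly while failing a class.** This needs a class of one or two images, and the mix is not given. With equal classes the individual score would visibly drop.
- **That Table 3 demonstrates the masking.** Its mean and median run across kits, whereas the planned ones most naturally run across CHWs. Its lowest mark belongs to an unused kit, which is not a photograph class, and some of its labels look inconsistent as printed. It also shows the authors reporting marks kit by kit.
- **That most images are easy, or that opposite errors cancel.** Nothing describes the difficulty of the images, and every error lowers the score.
- **That photograph accuracy would correct the field prevalence.** Twenty selected images are not the tests done in the field. The used kits, re-read by a technician or second observer, are the relevant data.

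**Conclusion.** The point holds in a limited form. The planned summary cannot separate missed positives, false positives and unrecognised invalid tests. That follows from the definition of percent correct and needs no assumption about the class mix. The size of the masking does depend on the unstated mix: an individual score of 95% or 90% with a failed class of one or two images, 80% with four, and 65 to 70% with equal classes. The 95.3% mean beside a 100% median rests on the further assumptions of 30 CHWs, two invalid images and 14 CHWs who misread both.

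The importance is modest. This is a descriptive analysis of one part of a secondary outcome, no threshold is attached to the photograph score, and the primary comparison is not touched. It merits a change because a more informative summary can be made from readings that are already collected.

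**What to change.** For each observation cycle:
- Report percent correct separately for positive, negative and invalid images, or give the 3 × 3 table of CHW reading against expert label.
- Attach 95% confidence intervals that allow for repeated readings by the same CHW.
- State how many of the 20 images are in each class.
- Keep the pooled mean and median as descriptive figures, and base the conclusion on reading accuracy on the class-specific results.

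For interpreting CHW-based prevalence, tabulate CHW result against technician re-reading for the used kits that are already being collected, in the same form, rather than relying on the photographs.

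The cost is a few more table rows and no new data collection. The drawback is that intervals will be wide for the smallest class, so little can be concluded about it if it holds only one or two images.
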